### Statistical analysis

For the sample calculation, reference will be made to compare sequenced RNAs, using a two-tailed Student's test for independent data. Considering the technology used to obtain RNA data [32], an expression variation of 6 (fold change) being expected, and assuming a gene coverage depth of 0.75 with a standard deviation of 1, a power of 80% and an alpha of 0.05 will be guaranteed by a sample of 11 subjects per group: 11 spontaneous BrS, 11 Suspected BrS (positive), 11 Suspected BrS (negative), 11 Control.

For bioinformatics analysis of transcriptomics, a case calling and demultiplexing will be performed raw processing data for both format conversion and demultiplexing by the Bcl2Fastq 2.20 version of the Illumina pipeline. Reads deduplication based on the unique molecular identifier (UMI) composed of 8 random bases for unambiguous identification of unique library molecules will discriminate between true PCR duplicates and independent adaptor ligation events to fragments with the same start site. DESeq2 will be used to perform comparisons between expression levels of genes and transcripts. Normalization will be performed using the median-of-ratios method [33]. An initial list of modulated genes in the current experimental set will be determined by applying a likelihood ratio test [34]. Adjusted *p*-value < 0.01 will be set an initial threshold. Further analyses on pairwise comparison will be obtained by filtration of the Fold Change (FC) calculation: the ratios between the relative expression values of two different conditions, expressed as the absolute value, will be assessed above 3.

Regarding the predictive models of Machine Learning, the sample numbers for the retrospective study (n = 300) and the final validation study (n = 100) correspond to the number of cases already classified by the clinical centers as Brugada syndrome, the former, and which can be collected during the experimental activities of the project by the same units, the latter. According to the activities foreseen in the trial, validation methodologies (cross-validation techniques) that will exploit this availability of data to develop and estimate the predictive models consistent with state of the art will be prepared [35].

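### The 80% power behind 11 per group is for one test at unadjusted alpha 0.05, but genes are selected at adjusted p < 0.01, where power is far lower

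*Protocol article*

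**What the plan says.** All the relevant text is in the Statistical analysis section of the protocol article.

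- **Planning.** The sample size refers to sequenced RNAs compared "using a two-tailed Student's test for independent data", with "an expression variation of 6 (fold change) being expected" and "assuming a gene coverage depth of 0.75 with a standard deviation of 1". The conclusion is that "a power of 80% and an alpha of 0.05 will be guaranteed by a sample of 11 subjects per group". The groups are "11 spontaneous BrS, 11 Suspected BrS (positive), 11 Suspected BrS (negative), 11 Control".
- **Analysis.** Expression is compared with DESeq2: "An initial list of modulated genes in the current experimental set will be determined by applying a likelihood ratio test". Then: "Adjusted *p*-value < 0.01 will be set an initial threshold". Pairwise comparisons are further filtered on fold change: "the ratios between the relative expression values of two different conditions, expressed as the absolute value, will be assessed above 3".

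The section does not connect the planning alpha with the analysis threshold and gives no power at the adjusted threshold. The machine-learning cohorts of 300 and 100 are justified by availability, so this is the only power statement in the article.

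**The concern.** Planning and analysis differ in three ways: the test (two-group t against likelihood ratio), the error rate (0.05 against 0.01), and the number of tests (one gene against a transcriptome with adjusted p-values). The error rate and the adjustment both make a gene harder to declare.

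The calculation supports secondary outcome 1 (biomarker identification). Secondary outcome 2, the risk system, uses those biomarkers. Under Study design and population, the validation phase tests the biomarkers found in the prospective phase, so a gene missed among the 44 subjects is not carried forward. A reader who trusts the stated 80% could take an empty or short gene list as good evidence that large expression differences are absent.

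**Working it through.** **Inputs from the protocol:** fold change 6 (ln 6 = 1.792), depth 0.75, SD 1, 11 per group, two-sided alpha 0.05, power 80%; analysis threshold adjusted p < 0.01.

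**Assumed, not in the protocol:** 15,000 independent genes, the share truly changed, Benjamini-Hochberg as the adjustment, and a likelihood ratio test across all four groups (3 df, chi-square approximation).

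**1. Reproduce the stated 11.** The depth input points to the usual RNA-seq formula, with the SD read as a coefficient of variation:

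n = 2(z₀.₉₇₅ + z₀.₈₀)² (1/depth + SD²) / (ln FC)² = 2 × 7.849 × (1.333 + 1) / 3.210 = 11.4.

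With 11 per group, SE(ln FC) = √(2 × 2.333/11) = 0.651. The standardised effect is 1.792/0.651 = 2.75, and power is Φ(2.75 − 1.96) = 78.6%. Of the variants tried, only two-sided unadjusted 0.05 with the depth term lands on 11. One-sided 0.05 gives 9.0, dropping the depth term gives 4.9, and an exact t-test needs 13.

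**2. Raw p < 0.01.** An adjusted p-value is never below the raw one, so this bounds the power from above. Pairwise power is Φ(2.75 − 2.576) = 57% (48% by exact t), and 80% would need 17 per group. For the four-group test, the noncentrality is 11 × Σ(deviations from the mean)²/2.333. That is 11.4 if one group differs and 15.1 if two differ from two, giving 62% and 79%.

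**3. Smaller per-gene alphas, 11 per group.** Detectable fold change (pairwise, 80% power) = exp[0.651 × (z + 0.842)].

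| Per-gene alpha | Pairwise | Four-group, one differs | Four-group, 2 v 2 | Detectable fold change |
|---|---|---|---|---|
| 0.05 | 79% | 82% | 92% | 6.2 |
| 0.01 | 57% | 62% | 79% | 9.3 |
| 0.001 | 29% | 35% | 54% | 15 |
| 0.0001 | 13% | 17% | 32% | 22 |

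**4. Benjamini-Hochberg at 1%.** The per-gene cut-off depends on how many genes are changed. The first three rows are simulated with 15,000 genes. The last solves α = 0.01 × [(1 − π)α + π × power(α)], where π is the changed share.

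| Truly changed | Pairwise | Four-group, one differs | Four-group, 2 v 2 |
|---|---|---|---|
| 15 (0.1%) | 2% | 3% | 9% |
| 150 (1%) | 3% | 6% | 21% |
| 1,500 (10%) | 15% | 22% | 47% |
| 50% (implausible) | 35% | 43% | 68% |

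**5. Pairwise n for 80% at this rule.** At 80% power the cut-off is α = 0.01 × π × 0.8 / [1 − 0.01(1 − π)]. For π = 10%, α = 0.00081 and n = 25.5, so 26 per group. For π = 1%, α = 0.00008 and n = 33.3, so 34.

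**6. Fold-change filter.** A gene with true fold change 6 shows an estimate above 3 with probability Φ((ln 6 − ln 3)/0.651) = 86%, so the filter cannot restore power.

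**7. Deeper coverage.** At an assumed depth of 10 with the same SD, the variance term falls to 1.1. Solving the step 4 equation for 0.1% to 10% changed gives four-group power of about 44% to 86% if one group differs and 76% to 97% for two against two.

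**The case against.** - **The arithmetic is sound at its own alpha.** This stands. The fault is a mismatch between two stated rules.
- **The planning formula is inferred.** The article names a t-test and cites a source that is not at hand. The close fit to 11 supports the inference but does not prove it. The mismatch itself needs no formula, since alpha 0.05 and adjusted p < 0.01 are both in the text.
- **The size depends on unstated quantities.** This stands for step 4: the gene count, the changed share and the adjustment method are not given. The direction of the loss, and the ceilings in step 2, do not depend on them.
- **The four-group test is not a handicap.** This stands. At equal alpha it is more powerful here than the pairwise test (82% to 92% against 79% at 0.05). The loss comes from the adjusted 0.01 threshold.
- **Depth 0.75 describes a thinly sequenced gene.** This stands, and step 7 shows how much better other genes do. But the protocol chose that depth for its power claim.
- **The outcome is secondary, the list is called initial, and a new cohort follows.** This is true, and the primary ECG outcome is unaffected. Validation guards against false positives and does not recover missed genes. The Limitations section concedes a possibly inadequate sample only for subgroup analysis.

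**Conclusion.** The concern holds. The stated 80% power applies to one gene, one pair of groups and unadjusted two-sided alpha 0.05, and the study will not select genes that way. On the protocol's own inputs, power under the planned threshold is at most 57% pairwise, or 62% to 79% for a four-group test, before any multiplicity penalty. With 1% to 10% of genes changed and false discovery held at 1%, it is about 3% to 15% pairwise and 6% to 47% for the four-group test. At depth 0.75 most genes with a true six-fold change would then be missed. The percentages after adjustment are illustrative because they rest on the assumed share of changed genes, independence between genes and the inferred variance formula. The shortfall against the promised power is not in doubt at the stated depth. Eleven per group remains defensible for discovery work. The power claim attached to it is wrong as written.

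**What to change.** Keep 11 per group and rewrite the sample-size paragraph:

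1. Remove the wording that promises the power. Say that 80% refers to a single pairwise test at unadjusted alpha 0.05.
2. Give power and the minimum detectable fold change for the rule actually used: the likelihood ratio test (stating whether it spans all four groups) at adjusted p < 0.01, with the adjustment method named. State the assumed number of genes and share truly changed, and show a range of depths.
3. Describe the 44-subject transcriptomic stage as exploratory discovery. State that a gene absent from the list has not been shown to be unchanged.

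The cost is one paragraph and one short simulation, with no extra patients and no change to the analysis. The stated power becomes less favourable.

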## Discussion

Difficulties still hamper the recognition of Brugada syndrome: first of all, the approach to asymptomatic patients since roughly 30% of the sudden death may represent the first manifestation of the disease [36]; moreover, ECG is by itself challenging due to temporal variability of the pattern and difficulties in selecting Br patients from other pathologies.

As far as disease characterization through biochemical markers, recently interesting results on autoantibodies against cardiac and skeletal alfa-actins, keratin-24, and connexin-43 in selected BrS patients have been published [37]. However, these results need to be confirmed in larger patient groups, especially in those with clear-cut Brugada pattern after administration of Na^+^ channel blockers.

Therefore, improvement in the ECG diagnosis of Brugada syndrome through artificial intelligence techniques, the definition of new biochemical markers from omics approach, and especially the combination of these markers with a well-tailored collection of clinical data may represent the key towards an unequivocal diagnosis in subjects without structural cardiac disease at risk of sudden cardiac death.

BrAID is a study intended to investigate the role of Machine Learning models to recognize specific ECG patterns associated with Brugada Syndrome, evaluate possible novel biomolecular markers of the syndrome, and integrate these data with the clinical ones in an advanced system for patient's risk stratification.

In particular, we will evaluate ML models and blood markers' power in recognition of Type 1 BrS syndrome patients with further advancement in recognition of spontaneous respect to drug-induced patients. The study will expand the current knowledge of Brugada Syndrome and will bring additional data on this disease and its clinical implications.

### Strengths

The present prospective multicenter study is designed to explore ML models' potential use in ECG analysis, transcriptomics, and their integration in BrS patients. It has clearly established aims, inclusion and exclusion criteria, as well as defined methods and endpoints.The trial is restricted to Type 1 BrS patients, excluding cardiac pathologies that could interfere with the effective recognition of diagnostic ECG patterns.Inclusion of positive and negative Ajmaline/Flecainide-induced BrS patterns cohorts will allow the investigation of patients with different risk profiles, supporting the ML algorithms and transcriptomics in a more effective sub-population recognition

## Limitations

The selected sample size may be inadequate to allow a subgroup analysis.The BrAID study purposefully excludes patients with structural cardiac diseases and comorbidities.

### Trial status

Participant recruitment will start in January 2021. The study completion will be in September 2023.

## Data Availability

Not applicable. Study patient enrolment and data collection are currently ongoing, and no datasets were generated for analysis yet.

## Abbreviations

BrS: Brugada syndrome
ECG: Electrocardiogram
ML: Machine learning
PES: Programmed electrical stimulation
SCD: Sudden cardiac death
SCN5A: Sodium voltage-gated channel alpha subunit 5
